### Analysis of economic data

Resource use and costs: Our trial population will have serious physical illness, with multiple hospital contacts for necessary physical treatments recommended by clinicians. It is therefore unlikely that hospital utilisation for physical reasons will differ significantly between the two arms, and this is therefore not being recorded to minimise patient burden. We will, however, record the number of contacts with community services, including mental health, especially as these are most likely to be influenced by our intervention. Therefore, the CSRI will be modified to collect data on community health services only. Resource utilisation will be multiplied by unit costs [57, 58] to estimate individual-level care-package costs for each patient at baseline and over the trial period. Costs related to the intervention will be included. We will calculate mean cost of CBT per participant, the incremental health and social care cost, the incremental QALY gain and incremental cost-effectiveness ratio. Results will be analysed on an intention-to-treat basis. Using multivariate regression methods, we will explore differences in costs and outcomes between treatment groups. We shall adjust for need-related factors, including functionality (assessed using BDI-II).

Bootstrapped incremental cost-effectiveness ratios and acceptability curves will be estimated in order to relate differences in costs and outcomes between the groups. Capturing benefits over a patient’s lifetime is an important issue, given outcome data will be missing at the end of the trial. We will use assumption-based modelling techniques [58] to explore the cost-effectiveness of the intervention using a lifetime horizon. In order to assess the key thresholds at which the intervention would be cost-effective, threshold analysis, for example, may be used as one method of framing assumptions around transition probabilities. The reliability of the model will depend on the quality and extent of missing data from the trial.

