**Methods:**

People aged 18 years and above with advanced cancer attending General Practitioner (GP), oncology or hospice outpatients from centres across England will be screened to establish a DSM-IV diagnosis of depression. Self-referral is also accepted. Eligible consenters will be randomised to a single blind, multicentre, randomised controlled trial of the addition to treatment as usual (TAU) of up to 12 one-hour weekly sessions of manualised CBT versus TAU alone. Sessions are delivered in primary care through Increasing Access to Psychological Care (IAPT) service, and the manual includes a focus on issues for people approaching the end of life. The main outcome is the Beck Depression Inventory-II (BDI-II). Subsidiary measures include the Patient Health Questionnaire, quality of life measure EQ-5D, Satisfaction with care, Eastern Cooperative Oncology Group-Performance Status and a modified Client Service Receipt Inventory. At 90 % power, we require 240 participants to enter the trial. Data will be analysed using multi-level (hierarchical) models for data collected at baseline, 6, 12, 18 and 24 weeks. Cost effectiveness analysis will incorporate costs related to the intervention to compare overall healthcare costs and QALYs between the treatment arms. We will conduct qualitative interviews after final follow-up on patient and therapist perspectives of the therapy.

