## Background

Depression is one of the most prevalent mental disorders in people with cancer [1]. It undermines the quality of life for individuals and those close to them [2], may reduce adherence to medication, and may prolong episodes of hospitalisation and increase healthcare costs [3]. Untreated depression is an independent predictor of early death in those with advanced cancer [4].

The prevalence of depression in people with cancer is around 10 % [5] and in advanced cancer may be as high as 21 % [6]. It is possible to treat depression effectively in the general population using antidepressant medication and psychological treatments such as cognitive behavioural therapy (CBT) and interpersonal therapies [7, 8]. However, it is not known whether these approaches are beneficial in those people with cancer who experience depression or those whose low mood exceeds what might be expected in the face of life-limiting illness. A recent systematic review of randomized controlled trials of the efficacy of any treatment intended to reduce depression in adults with diagnoses of both cancer and depression found that only seven relatively small trials have been published [9].

A meta-analysis in 2008 [10] suggested that CBT may be a promising approach [11], although a recent systematic review of interventions for depression in cancer, patients of which are a poor prognostic group, did not generate any well-designed trials where a CBT intervention was used [9]. Indeed, all currently published trials in this field having methodological limitations [10, 12, 13]. The use of specially trained nurses to use CBT skills in palliative care has not been shown to alleviate depressive symptoms in cancer [14]. Whilst some benefit may exist for nurse-led problem solving therapy and behavioural activation for depression in advanced cancer [9], the effectiveness of CBT remains to be evaluated. Evidence exists from qualitative studies with people receiving hospice care that CBT is acceptable [15], but no studies have explored the therapists’ experience of delivering CBT in this context.

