### Measure of service utilisation

#### Client Service Receipt Inventory

The Client Service Receipt Inventory (CSRI) is a short modified version of the CSRI [48], which collects data directly from participants on use of hospital services, day centres, residential homes, rehabilitation centres, paramedic/ambulance, community nurses, occupational/physio therapists, and local GP/practice nurses, as well as social care/social housing use.

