## Discussion

This trial will provide robust evidence on the effectiveness and cost-effectiveness of individual cognitive behaviour therapy for treating people with advanced cancer and depressive disorder. Cancer will affect one in three of the UK population during their lifetime, and it remains one of the commonest causes of death. In caring for people with advanced cancer, much effort may be expended on addressing treatments for physical problems including the management of symptoms such as pain, nausea and fatigue that are common as health deteriorates. Good supportive care at this time should include accurate assessments of mental health, and diagnosis and treatment for depression when necessary. If found to be effective, use of talking therapies may enhance the experience not only of those people facing advanced cancer but also those close to them.

This trial will generate data to aid our understanding of the feasibility of delivering CBT to a population with deteriorating physical health in the community through the existing network of IAPT therapists. We shall gain information on the interfaces between oncology services in secondary care, CBT in primary care and the hospice in the third sector. Some day care services provided through hospices have the capacity to offer talking therapies within current models of care [59, 60]. Evidence from this trial may inform the likely benefits of strengthening these services within palliative care, as well as assess whether augmenting usual care with CBT is cost-effective based on the National Institute for Health and Care Excellence threshold.

Analyses of the content of therapy sessions will enhance our understanding of the issues of importance to people with advanced cancer who experience depression. Our data may reveal domains of worry and psychological need in those facing the approach of death with which we are not yet familiar. Such new knowledge may enable the development of recommendations and guidance for therapists providing CBT in this context, and for the wider clinical community caring for people with cancer for whom cure is not likely.

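### The protocol contradicts itself on whether the modified CSRI records hospital use; if it does not, the cost comparison cannot be called one of overall healthcare costs

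*Protocol article*

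**What the plan says.** Two sections of the protocol article describe the resource-use form.

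- **Client Service Receipt Inventory** (under Measure of service utilisation): the form, already described as a short modified version, "collects data directly from participants on use of hospital services, day centres, residential homes", together with rehabilitation centres, ambulance, community nursing, therapists, primary care, and social care or social housing.
- **Analysis of economic data**: the premise is stated first, namely "It is therefore unlikely that hospital utilisation for physical reasons will differ significantly between the two arms". From this the section draws its decision about such use: "and this is therefore not being recorded to minimise patient burden". It adds that "the CSRI will be modified to collect data on community health services only". The same paragraph then lists as outputs "the incremental health and social care cost, the incremental QALY gain and incremental cost-effectiveness ratio".

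The Abstract (Methods) says the cost-effectiveness analysis will serve "to compare overall healthcare costs and QALYs between the treatment arms". The Discussion expects the trial to help assess whether adding CBT is "cost-effective based on the National Institute for Health and Care Excellence threshold". Cost effectiveness is part of the hypothesis and one of the two stated objectives.

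**The concern.** A reader cannot tell from the protocol which costs enter the incremental cost-effectiveness ratio (ICER). Under the CSRI section, hospital and social care are in. Under the economic section, hospital care is out, and social care has no stated data source although it is named in the numerator.

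If the narrower description is the true one, three things follow. The quantity estimated is not the one the Abstract announces. The omission rests on an assumption of equal hospital use that the data could not check. And the bootstrapped ICERs and acceptability curves would carry no uncertainty from hospital cost, so for an overall-cost question they would look too precise. The planned lifetime model would inherit the same gap.

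The assumption also sits uneasily with the Background, which says that depression "may prolong episodes of hospitalisation and increase healthcare costs".

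**Working it through.** **Step 1: compare the sections.** The protocol states no incremental cost, QALY gain or ICER, so there is no planned figure to reproduce. The check is mainly of the text.

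| Item | CSRI section | Analysis of economic data |
|---|---|---|
| Hospital services | collected | use for physical reasons not recorded; form limited to community health services |
| Residential homes, ambulance | collected | not within a form limited to community health services |
| Social care | collected | outside that limit, yet part of the planned numerator |

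The sentence on not recording is restricted to use for physical reasons. The later restriction of the form to community health services has no such qualifier and, read literally, excludes all hospital use. The economic section is also inconsistent with itself on social care.

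**Step 2: what the omission does.** Write the full incremental cost (CBT minus TAU) as

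ΔC = ΔC(therapy) + ΔC(community and social) + h,

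where h is the between-arm difference in mean hospital cost. Leaving hospital care out sets h = 0. The error in the incremental cost is h, and the error in the ICER is h / ΔQALY. Frequent hospital contact in both arms does not make h zero; only equal mean cost does. With no hospital data, h cannot be estimated.

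**Step 3: illustration of scale.** Inputs:

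- Therapy cost £750: the Background figure for standard IAPT therapy, assumed to apply here.
- Threshold £20,000 per QALY: from the Background.
- Difference in community and social care cost: assumed zero.
- h = −£300, £0 or +£300: assumed, not a hospital figure from the protocol.
- QALY gains of 0.02, 0.0375 and 0.05: assumed.

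Break-even QALY gain = (750 + h) / 20,000:

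- h = 0: 750 / 20,000 = 0.0375
- h = −300: 450 / 20,000 = 0.0225
- h = +300: 1,050 / 20,000 = 0.0525

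The shift is 300 / 750 = 40% either way.

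ICER = (750 + h) / ΔQALY:

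| ΔQALY | h = −£300 | h = £0 | h = +£300 |
|---|---|---|---|
| 0.02 | £22,500 | £37,500 | £52,500 |
| 0.0375 | £12,000 | £20,000 | £28,000 |
| 0.05 | £9,000 | £15,000 | £21,000 |

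At 0.02 QALY no value of h in this range brings the ICER below £20,000. At 0.05 QALY, +£300 takes it just above. A £300 difference therefore changes the conclusion only if the QALY gain lies between 0.0225 and 0.0525.

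**The case against.** The strongest defence is that the omission is a reasoned choice. Patients with advanced cancer have many hospital contacts for necessary treatment, extra questions are a burden, and costs that are equal on average cancel in an incremental comparison. The economic section also expects community contacts to be the ones most influenced by CBT. This stands as a reason for a narrower perspective. It does not justify the label of overall healthcare costs, and it does not remove the conflict with the CSRI section.

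Four stronger readings are tempting but are not supported:

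- **That the planned ICER certainly omits hospital care.** This follows only if the economic section describes the form in use. If the CSRI section does, the data exist and only the economic text needs correcting.
- **That the Background contradicts the equal-use assumption.** It says only that depression may prolong hospital episodes. The economic section says a difference between arms in use for physical reasons is unlikely. Both can be true; there is tension, not contradiction.
- **That the protocol itself supplies a £300 hospital effect.** The Background does cite a £300 NHS saving, but it is for standard IAPT therapy for depression and anxiety, given in the context of the first 2 years. It is not specific to hospital care, advanced cancer or 24 weeks, and no source supports an increase of that size.
- **That the omission would reverse the trial's verdict.** No expected QALY gain is given, so there is no verdict to reverse.

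It is also fair that the NICE comparison appears as an aim in the Discussion, not as a formal decision rule.

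**Conclusion.** The contradiction between the two sections is certain and leaves the cost numerator of a stated objective undefined. The consequence for the ICER is conditional. If the form covers community health services only, the result is an intervention-plus-community-cost ratio. It is unbiased for overall healthcare cost only under equal mean hospital costs, an assumption the trial could not examine.

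The possible size is not known from the protocol. Under the assumptions shown, a £300 difference moves the break-even gain by 0.015 QALY in either direction from 0.0375, which matters only for gains between 0.0225 and 0.0525.

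This should be fixed, but it does not threaten the trial: the primary BDI-II analysis and the sample size do not depend on it.

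**What to change.** First establish which section describes the form in use, and make the two agree.

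- **If hospital services are on the form:** correct Analysis of economic data and include them in the costs.
- **If they are not:** correct the CSRI section. State the perspective as the intervention plus the community health services, and any social care, actually collected. Remove the reference to overall healthcare costs. State equal mean hospital cost between arms as an assumption. Add a sensitivity analysis over a range of h, fixed before unmasking, and qualify the NICE comparison accordingly.

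A useful summary for that sensitivity analysis is the switching value, h* = 20,000 × ΔQALY − ΔC(recorded). With the illustrative £750, h* is £250 at 0.05 QALY (1,000 − 750) and −£350 at 0.02 QALY (400 − 750). The reader can then judge whether a hospital cost difference of that size is plausible. It fits the threshold analysis that the protocol already mentions.

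The cost is a few sentences, a little more analysis and a less sweeping cost-effectiveness claim. No new data collection is required. Adding hospital items now, if they are absent, would leave incomplete costs for earlier participants, since recruitment began on 19 September 2012.

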### Primary outcome

***Beck Depression Inventory-II*** (BDI-II; [37].

This is a 21-item self-report measure with a maximum score of 63 indicating severe depressive symptoms. It contains few items measuring affective-somatic symptoms, with 15 of the 21 items assessing negative cognitions, which are a target of cognitive interventions. The psychometric properties of the BDI-II are similar to the BDI [38], which is the most widely used self-report instrument for depressive symptoms and has also been used in trials of psychotherapy for people with advanced cancer [13, 39, 40]. The BDI-II also has a number of cognitive elements that are particularly useful for measuring change with CBT.

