#### Eastern Cooperative Oncology Group-Performance Status

The Eastern Cooperative Oncology Group-Performance Status (ECOG-PS) [47] is a scale measuring physical functioning on five levels: 0, asymptomatic normal activity; 1, symptomatic but fully ambulatory; 2, symptomatic and in bed less than 50 % of time; 3, symptomatic and in bed more than 50 % of time; 4, 100 % restricted to bed.

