### Power

(i) *Clinical effectiveness*: Our primary outcome is an overall effect of treatment over the 24-week period of follow-up. We have powered the study to enable detection of a difference in BDI-II of six points (standard deviation 12) between the TAU and CBT groups measured at 12 weeks, assuming a treatment effect of three points after 6 weeks, and a sustained six-point difference after 18 and 24 weeks (Table 1). We have been cautious in assuming a sustained rather than an increasing treatment effect after 12 weeks. Follow-up at 12 weeks post-baseline in other trials ranges from 44 % [14] to over 75 % [12, 13]. Although our client group may be in the last year of life, we do not plan to recruit people who are about to die. We will assume a 70 % follow-up rate after 6 weeks, decreasing to 65 % at 12 weeks and 60 % after 24 weeks (Table 3).

The BDI-II manual reports that the correlation between BDI-II values from sessions 1 week apart is 0.93 (Beck and Steer [37]). To estimate the correlation between measurements 6 weeks apart, the simplest assumption possible is that future values will depend only on the most recent past, and not on any history prior to that (in technical terms, this is called an ‘autoregressive process of order 1’). Then, the correlation between measurements will decay at a constant rate of 0.93 per week, and our best estimate of the correlation between BDI-II measures taken 6 weeks apart is 0.93^6^ = 0.65.

Assuming the attrition rates and correlation reported above, the sample size required to detect an overall difference between the groups, at 90 % power and 5 % significance is 109 participants per trial arm (using a multi-level model adjusting for baseline BDI-II). To account for clustering by therapist, the sample size needs to be inflated by a factor of 1.10. (1 + (average cluster size -1) × intra-class correlation coefficient). This is based on an intra-class correlation coefficient of 0.02 [54, 55] and an average of six participants per therapist post-intervention. We therefore intend to recruit 120 participants per trial arm, with the expected numbers available at each follow-up given in Table 1.

An important secondary outcome is to assess how the treatment effect changes over time.

The proposed sample size will provide 90 % power to detect a six-point difference in BDI-II at 12 weeks and 80 % power to detect a six-point difference at 24 weeks if attrition rates are as stated in Table 3.

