### Analysis plan

Clinical data: Analysis of data will be undertaken according to CONSORT guidelines within PRIMENT Clinical Trials Unit. A flow chart will present the follow-up rate for each group, with the reason for non-completion of the BDI-II score. Descriptive results (mean and SD) for demographic and pre and post-treatment BDI-II scores at each follow-up period will be presented by treatment group. Analyses will be on an intention-to-treat basis using multi-level (hierarchical) models. The levels of hierarchy in the data are as follows: first level - repeated measures, second level - participants, and third level - therapist. The primary analysis will test for an overall treatment effect on an intention-to-treat basis using BDI-II over the four follow-ups, controlling for baseline BDI-II score and other baseline confounders, including antidepressant dose. A secondary analysis will also look at the effect of treatment separately at each time point, by including a treatment-time interaction in the multi-level model. A complier average causal effect (CACE) analysis will be performed to take into account the possible lack of adherence to CBT. Analyses will be performed using the current version of STATA (version 13) [56].

Antidepressants will be monitored in order to compare their use between groups to check that they are similar. This will be done by recording all antidepressants prescribed during the trial (name, dose and frequency). This will include SSRIs and other antidepressants such as tricyclics, which are often used in small doses for symptom control in end-of-life care. We will convert antidepressant dose for any drug into a mean equivalent dose of imipramine following a method we used in another trial of CBT for depressed older people [28].

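### The economic regressions name the BDI-II as the measure of functionality, though it is the primary depression outcome; the functioning scale (ECOG-PS) is not named and no time point is given

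*Protocol article*

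**What the plan says.** Cost effectiveness is one of the trial's two objectives. In Analysis of economic data the protocol article states: "Using multivariate regression methods, we will explore differences in costs and outcomes between treatment groups". It then describes the adjustment: "We shall adjust for need-related factors, including functionality (assessed using BDI-II". No visit is attached to the BDI-II there, and the ECOG-PS does not appear in that section.

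Elsewhere the two instruments are described differently. Under Primary outcome, on the BDI-II: "This is a 21-item self-report measure with a maximum score of 63 indicating severe depressive symptoms", and further, "with 15 of the 21 items assessing negative cognitions, which are a target of cognitive interventions". Under Secondary outcomes, the ECOG-PS "is a scale measuring physical functioning on five levels". Table 2 schedules the BDI-II at all five visits and the ECOG-PS at baseline, 12 and 24 weeks.

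The clinical model in Analysis plan does fix the time point: "controlling for baseline BDI-II score and other baseline confounders, including antidepressant dose".

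**The concern.** Two things are unsatisfactory in the one sentence.

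First, the construct and the instrument do not match. A health economist following the sentence literally would enter a depression score and report an adjustment for functioning. The scale that the trial collects for functioning would be used only if the analyst added it unprompted.

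Second, the variable named is the one that CBT is meant to change, and it is measured four times after randomisation. With no time point given, the sentence permits a follow-up BDI-II covariate. That would condition the arm comparison on a consequence of treatment. The QALY difference would lose the part that comes from improved mood, which is the main route by which the intervention is expected to work.

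**Working it through.** **1. The plan's own figures.** The economic section states no number to reproduce. The trial's sample size does reproduce: the design effect is 1 + (6 − 1) × 0.02 = 1.10, and 109 × 1.10 = 119.9, so 120 per arm. This point concerns a covariate and leaves that figure unchanged.

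**2. Instrument against construct.**

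| | BDI-II | ECOG-PS |
|---|---|---|
| What the protocol says it measures | depressive symptoms; 15 of 21 items on negative cognitions | physical functioning, levels 0 to 4 |
| Role | primary outcome | secondary outcome |
| Visits (Table 2) | baseline, 6, 12, 18, 24 weeks | baseline, 12, 24 weeks |
| Named in the economic analysis | yes, as functionality | no |

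Nothing in the protocol describes the BDI-II as a measure of functioning.

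**3. What each time point would do.** Inputs from the Power section: "detection of a difference in BDI-II of six points (standard deviation 12) between the TAU and CBT groups measured at 12 weeks", and "assuming a treatment effect of three points after 6 weeks, and a sustained six-point difference after 18 and 24 weeks". Inputs assumed, because the documents give none: utility falls by *b* per BDI-II point, and CBT may add a direct utility effect *c* that does not pass through depression. At 12 weeks:

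utility = constant − *b* × BDI-II(12 weeks) + *c* × arm + error

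- No adjustment: arm effect = 6*b* + *c*.
- Adjusted for baseline BDI-II: arm effect = 6*b* + *c*. Baseline is independent of the randomised arm, so nothing is lost.
- Adjusted for 12-week BDI-II: arm effect = *c*. The 6*b* is removed.

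With *b* = 0.005, 6*b* = 0.030. A regression on 400,000 simulated participants (BDI-II SD 12; correlation between baseline and 12 weeks 0.93^12 = 0.42, from the protocol's autoregressive assumption) agrees with the algebra up to simulation error:

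| Covariate | *c* = 0: formula | simulated | *c* = 0.02: formula | simulated |
|---|---|---|---|---|
| none | 0.030 | 0.0296 | 0.050 | 0.0491 |
| baseline BDI-II | 0.030 | 0.0296 | 0.050 | 0.0490 |
| baseline and 12-week BDI-II | 0 | −0.0004 | 0.020 | 0.0192 |

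The loss is 6*b* whatever the value of *c*: 6 × 0.002 = 0.012 up to 6 × 0.010 = 0.060. Because the plan assumes that the six points persist, the same arithmetic applies at 24 weeks, the other follow-up visit with EQ-5D, if 24-week BDI-II were the covariate.

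**4. Costs.** The incremental cost is the CBT delivery cost plus any change in other service use. The protocol includes intervention costs. Delivery cost follows from allocation and attendance, not from the change in BDI-II, so it would survive adjustment for follow-up BDI-II. Only a change in service use brought about by mood could be removed. If that change were a saving, removing it would raise the incremental cost.

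**5. Leaving ECOG-PS out.** In a randomised comparison, omitting a baseline covariate does not bias the arm difference. It gives up some precision and some protection against chance imbalance. The documents give no correlation of ECOG-PS with cost or utility, so the loss cannot be sized.

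**The case against.** The strongest reply is that this is a loose word in a condensed article. The context points to baseline: the clinical model names baseline BDI-II, need-related factors are normally measured at entry, and the economic section refers to baseline costs and to intention to treat. Covariate timing is commonly left to the analysis plan, which is not shown. The regressions are introduced as exploring differences, and the section does not say that the bootstrapped ratios or the acceptability curves carry this adjustment.

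Much of this stands. A missing time point alone would hardly deserve a comment, and an undated covariate is not evidence that follow-up values will be used. The reply does not reach the instrument, however. Naming a depression scale as the measure of functionality is a statement in the text, at odds with the protocol's own descriptions. It is not a detail deferred to another document. Since the sentence has to be rewritten for that reason, the time point can be settled in the same edit.

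Three stronger readings are tempting, and the document supports none of them:

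- A reader might infer that the CBT effect will be adjusted away. That requires follow-up BDI-II, which the text neither states nor rules out.
- A reader might infer that physical function goes unadjusted. The list is opened with the word *including*, so ECOG-PS is unnamed, not excluded.
- A reader might infer that the cost difference is pulled toward zero. Step 4 of the working shows that this does not follow; with a positive net cost, removing a saving would move it away from zero.

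**Conclusion.** The point holds in a limited form. The sentence is wrong as written on the instrument: the BDI-II is the primary depression outcome, and the scale for functioning is the ECOG-PS. It is also unclear on timing. If baseline BDI-II is meant, there is no bias, and the stated adjustment for functioning is simply not delivered by the named scale. If follow-up BDI-II were used, the arm effect on utility would lose 6 × *b* at a visit: 0.030 at an assumed slope of 0.005, with a range of 0.012 to 0.060.

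These sizes rest on the planned 6-point effect and on an assumed slope that is not in the documents. They also assume that nothing else drives both follow-up BDI-II and utility; where worsening illness does so, the adjusted estimate would not be a clean direct effect either. That the estimate falls to zero when *c* = 0 follows from assuming that all benefit passes through depression, and should not be read as a forecast. A standardised effect size would need a correlation between BDI-II and utility, which the documents do not give.

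The sentence should be corrected before the economic analysis is run. The primary clinical analysis and the sample size are not touched.

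**What to change.** Replace the sentence in Analysis of economic data with wording such as:

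> The cost and QALY regressions will adjust for baseline need-related factors: functioning (baseline ECOG-PS), depression severity (baseline BDI-II), the baseline value of the dependent variable (EQ-5D utility for QALYs, CSRI cost for costs) and the antidepressant stratification factor. No post-randomisation variable will be a covariate.

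The ECOG-PS entry and the baseline restriction correct the text. The baseline value of the dependent variable and the stratification factor are an improvement that comes free with the same edit, not the repair of a stated error. The last clause also keeps the 12- and 24-week ECOG-PS out of the model. The cost is one sentence: Table 2 schedules ECOG-PS, BDI-II, EQ-5D, CSRI and antidepressant use at baseline, so nothing further has to be collected.
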